## Abstract

**Background:**

Effective antiretroviral therapy (ART) in people living with HIV (PLWH) has improved life expectancy and increased risk of age-associated cardiometabolic comorbidities. At-risk alcohol use is more frequent among PLWH and increases the risk of health challenges. PLWH with at-risk alcohol use are more likely to meet criteria for prediabetes/diabetes and this is associated with impaired whole-body glucose-insulin dynamics.

**Methods:**

The Alcohol & Metabolic Comorbidities in PLWH: Evidence Driven Interventions Study (ALIVE-Ex Study, NCT03299205) is a longitudinal, prospective, interventional study to determine the effects of an aerobic exercise protocol on improving dysglycemia among PLWH with at-risk alcohol use. The intervention is a moderate intensity aerobic exercise protocol implemented 3 days per week for 10 weeks at the Louisiana State University Health Sciences Center-New Orleans. Participants who have a fasting blood glucose level between 94 and 125 mg/dl will be enrolled in the study. Oral glucose tolerance tests, fitness assessments, and skeletal muscle biopsies will be performed pre- and post-exercise intervention. The primary outcome is to determine whether the exercise protocol improves measures of whole-body glucose-insulin dynamics, cardiorespiratory fitness, and skeletal muscle metabolic and bioenergetic function. Secondary outcomes are to determine whether the exercise intervention improves cognitive function and overall quality of life. Results generated will demonstrate the effect of exercise on glycemic measures in PLWH with subclinical dysglycemia and at-risk alcohol use.

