### Screening

After informed consent, participants are instructed to fast and not drink alcohol overnight. Participants are considered eligible if they have a fasting blood glucose of 95–124 mg/dL, measured by a single-use auto-disabling finger stick device and glucose meter (True Metrix® Pro Blood Glucose Monitoring System, McKesson).

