### Data management and analysis

All data are entered into REDCap and are handled with confidentiality. Personal information of participants such as phone number and email addresses are used only to contact the participant. Names of participants appear only in the demographic form. The participants’ demographic and outcome measures of interest pre- and post-exercise intervention will be summarized using descriptive statistics. Mean, standard deviation, and range will be calculated for continuous variables, and frequencies and percentages will be generated for categorical variables. For continuous variables (such as VO_2max_, OCR, ECAR), the normal distribution assumptions will be tested. If necessary, the data will be transformed to follow the normal distribution assumption. If the normality assumption cannot be met, these variables will be classified as categorical or analyzed using non-parametric tests. For categorical variables (e.g., glucose at 2 h, HOMA-IR, HOMA-b) clinical cutoff values will also be used. The changes in the outcome measures (e.g., OGTT outcomes, bioenergetic measures, microRNA expression, RHR, VO_2max_, MOCA measures, ASA24 measures) between pre and post exercise intervention will be tested using the paired t-test. Linear regression models will also be used to analyze the relationship between alcohol use with the outcome measure changes as the dependent variable, adjusting for potential confounding factors (such as age, sex, race, viral load and CD4 counts). If there is matching or balance achieved, age and gender will be used as categorical variables rather than confounders. A p < 0.05 will be used for statistical significance.

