## Results

The first phase of the study that determined whether PLWH with at-risk alcohol use had increased risk of dysglycemia and dysregulated muscle metabolic function are published.Results indicate that in response to an oral glucose tolerance test (OGTT) in PLWH with fasting dysglycemia; participants with at-risk alcohol use were five times more likely to meet criteria for prediabetes/diabetes. At-risk alcohol use was negatively associated with fasting C-peptide levels, increased odds of decreased HOMA-β, and increased 2-h glucose values [32]. These changes in whole body glucose insulin dynamics were also associated with skeletal muscle mitochondrial bioenergetic dysfunction.Bioenergetic health index (BHI), a positive indicator of mitochondrial bioenergetic health, was lower, and non-mitochondrial oxygen consumption was higher with increasing AUDIT scores. Proton leak, indicating decreased ATP synthesis, was significantly associated with higher 2-h glucose levels and AUDIT score, and myoblast mitochondrial volume was positively associated with the interaction between 2 h glucose and AUDIT. In addition, expression of genes associated with lipid handling were significantly decreased with the interaction of 2-h glucose and AUDIT, and expression of genes controlling mitochondrial biogenesis and dynamics were significantly decreased with higher 2-h glucose levels and AUDIT scores, respectively [33]. All these findings indicate that skeletal muscle mitochondrial health and bioenergetic function are dysregulated with at-risk alcohol use and dysglycemia.We were also able to demonstrate that recent alcohol use (PEth) influenced associations between circulating microRNAs implicated in metabolic function. Expression of miR-206 (muscle enriched) was significantly lower, and expression of miR-let-7b and miR-146a (adipose enriched) were significantly higher in PLWH with positive PEth. Participants with no recent alcohol use had miR-133a (muscle enriched) and miR-221 (adipose enriched) expression levels associated with altered glucose/insulin dynamics. While in participants with positive PEth, miR-20a (liver enriched) and miR-375 (pancreas enriched) together strongly predicted increased 2 h glucose levels [34]. Thus, results indicate that associations between circulating miRs and measures of glucose/insulin dynamics are modulated by alcohol use suggesting unique pathophysiological mechanisms contributing to altered glucose homeostasis in PLWH.

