At the time of submission of the manuscript, the second phase of the study is ongoing. Based on prescreening, or preliminary eligibility from the parent NOAH study, 395 PLWH were assigned an ALIVE-Ex specific ID, out of whom 318 came for consent visits. Of the 242 consented, 155 met eligibility criteria. The general demographics of the participants enrolled are shown in Table 2. One hundred and fifty-two (152) participants underwent pre-exercise OGTT and of these, 84 subjects underwent medical clearance. Sixteen subjects did not fulfill eligibility criteria as shown in Table 3. Sixty-three pre-muscle biopsies were performed and as of November 2022, 33 participants have completed exercise, post intervention fitness assessments, OGTTs and muscle biopsies.

**Table 2 Tab2:** Demographic Parameters of the ALIVE-Ex Study

Demographics	(n = 155)
	% (n)
Sex	
Female	31.6(49)
Male	69 (107)
Race	
African American	76.8 (119)
White	20.6 (32)
Other	1.9 (3)
Age, years	
20 to 30	6.4 (10)
31 to 40	14.2 (22)
41 to 50	18 (28)
51 to 60	45.8 (71)
60 +	15.4 (24)
Income	
< $20,000	84.5 (131)
$20,000 to $39,999	9 (14)
$40,000 +	6.4 (10)
Education	
< High School	34.8 (54)
High School Graduate	28.3 (44)
Some College, Junior/Community College, Vocational/Trade School	26.4 (41)
4-year College/Graduate/Professional School	10.3 (16)

**Table 3 Tab3:** Reasons for being ineligible for exercise of the ALIVE-Ex Study

Reason for ineligibility	Number
Active cocaine or amphetamine use	9
Angina	1
Lidocaine allergy	1
Uncontrolled hypertension	3
Orthopedic complications	2
Total	16

We anticipate that the exercise intervention will result in an increase in cardiorespiratory fitness reflected as decreased Resting Heart Rate (RHR) and increased VO_2max_. We also anticipate that the exercise intervention will improve OGTT outcome measures. We predict that the exercise will positively impact muscle bioenergetic measures and this will associate with overall changes in glycemic measures. We anticipate that exercise will have the greatest impact on these outcome measures in people with at-risk alcohol use. Although the intervention’s objective was not to improve other lifestyle choices such as diet and alcohol use, the analysis will identify whether exercise changes dietary patterns and alcohol use. It will also identify whether there is an improvement in cognitive measures and overall quality of life.

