## Discussion and conclusions

PLWH have a high prevalence of physical inactivity, increased risk of cardiometabolic comorbidities [1–5], and at-risk alcohol use [41]. This is compounded by significant health disparities associated with race, ethnicity, socioeconomic status, and geographic location [42, 43]. Exercise is an effective intervention to improve cardiometabolic health across all populations [23, 44–46]. Studies also suggest that people with substance use disorders, when provided with structured exercise interventions derive general health benefits [47–51]. Results from our preclinical [14, 15, 52, 53] and clinical studies and from the first phase of this intervention study [32–34] indicate that PLWH with at-risk alcohol use have metabolic dysregulation.

The ALIVE-Ex study will be the first study that will determine the impact of a moderate intensity aerobic exercise intervention on metabolic health among PLWH with at-risk alcohol use. Not only will the participants derive direct benefits from the exercise regimen, but the results generated will provide knowledge on the effect of exercise on glycemic measures and muscle bioenergetic adaptations in people with subclinical dysglycemia. The proposed intervention will also have the potential to be scalable and our hope is that it may be recommended to promote lifestyle changes among PLWH particularly in underserved communities.

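### The article attributes the exercise result to PLWH with at-risk alcohol use, but entry has no at-risk criterion and no stated analysis gives the mean change in at-risk participants

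*Protocol article*

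**What the plan says.** **Population named.** The abstract (Methods) gives the aim as "to determine the effects of an aerobic exercise protocol on improving dysglycemia among PLWH with at-risk alcohol use" and says the results will show the "effect of exercise on glycemic measures in PLWH with subclinical dysglycemia and at-risk alcohol use". One sentence in the Background describes the study in the same terms. The Discussion says the study will be the first to determine the "impact of a moderate intensity aerobic exercise intervention on metabolic health among PLWH with at-risk alcohol use".

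**Population enrolled.** The abstract's entry rule is "Participants who have a fasting blood glucose level between 94 and 125 mg/dl will be enrolled in the study". The Screening section says "Participants are considered eligible if they have a fasting blood glucose of 95–124 mg/dL". Table 1 adds age, the PAR-Q and a list of exclusions. Its only alcohol item excludes acute intoxication on a visit day. Medical clearance adds cardiovascular, neuropathy and stimulant-use conditions. None of these sets an AUDIT, TLFB or PEth threshold. (The fasting glucose limits also differ between places and must be reconciled, but that is a separate point.)

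**Analysis.** Under Data management and analysis, changes in the outcomes "between pre and post exercise intervention will be tested using the paired t-test", with no alcohol subset named. Linear regressions of change on alcohol use, adjusted for potential confounders, are planned as well.

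**Expectation.** The Results section states: "We anticipate that exercise will have the greatest impact on these outcome measures in people with at-risk alcohol use".

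**The concern.** The population in the claim is narrower than the population that can enter, and the pre-post test is not restricted to the narrower one. That would matter little if alcohol use did not affect the response, but the article expects that it does. A pooled change reported as the result in at-risk drinkers could then understate their change, or could owe part of its size to people who are not at-risk drinkers. A reader could not tell which.

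**Working it through.** The article gives no sample size, power, effect size or SD, so there is no figure of its own to reproduce. The mismatch follows from reading the text. The arithmetic below only shows how much it could matter.

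**Step 1. Is the sample mixed?** Every eligibility statement (abstract, Table 1, Screening, Medical clearance) lacks an at-risk criterion. AUDIT and TLFB are completed during the OGTT, as measures. Both the expectation of a greatest impact in at-risk users and the regression on alcohol use presuppose that alcohol use varies among participants. So the plan allows a mixed sample.

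**Step 2. What does the pooled change estimate?** Let s be the at-risk share, d1 the mean change in at-risk participants and d0 the mean change in the others.

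- Pooled change = s·d1 + (1 − s)·d0.
- Ratio to the at-risk change = s + (1 − s)·(d0/d1).

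The ratio is 1 only if d0 = d1 (or s = 1).

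**Step 3. Inputs.** s = 0.57 is the at-risk share in the parent NOAH cohort (Background). The trial's own share is not given and recruitment went beyond NOAH from 2018, so 0.57 is an assumption and 0.40–0.70 is shown as a range. The article reports 33 completers as of November 2022. Alpha is 0.05, assumed two-sided.

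| Response of the others | s = 0.40 | s = 0.57 | s = 0.70 |
|---|---|---|---|
| None (d0 = 0) | 40% | 57% | 70% |
| Half (d0 = d1/2) | 70% | 78.5% | 85% |
| Equal (d0 = d1) | 100% | 100% | 100% |

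For example, 0.57 + 0.43 × 0.5 = 0.785.

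**Step 4. Power, for an at-risk change of 0.5 SD.** 0.57 × 33 ≈ 19 at-risk, leaving 14 others. Power comes from the noncentral t distribution with noncentrality d·√n.

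- Pooled, d0 = 0: 0.57 × 0.5 = 0.285, n = 33, power 35.5%. With 19/33 in place of 0.57 it is 36%. Simulation gives 34%, because the difference between the groups adds to the SD of the pooled changes.
- Pooled, d0 = half: 0.785 × 0.5 = 0.3925, n = 33, power 59%.
- Pooled, d0 = d1: 0.5, n = 33, power 80%.
- At-risk mean from 19 participants: 54%, or 56% if the residual variance is taken from both groups (31 df).

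The at-risk estimate has more power than the pooled test when the others do not respond, slightly less when they respond half as much, and clearly less when the groups respond alike.

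**Step 5. Precision cost.** The detectable standardised change at 80% power is 0.50 SD with all 33. It is 0.68 SD with 19 at-risk (0.85 SD with 13 at s = 0.40, 0.61 SD with 23 at s = 0.70).

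**Step 6. Does the planned regression supply the estimate?** It relates change to alcohol use, so it addresses effect modification. As stated it has no at-risk cut-off, and its alcohol coefficient is the difference in change per unit or category of drinking. That is not the mean change in at-risk participants.

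**The case against.** The strongest reply is that alcohol use is not ignored. A regression of change on alcohol use is already planned, with adjustment for confounders, and it is the natural tool for effect modification. The article also does not rank the paired t-test above the regression. The overall Phase 2 objective in the Background names no alcohol subgroup, and an all-participant paired test suits it. Pooling itself is inferred from the absence of a named subset. All of this stands, and it narrows the point to two gaps: the population wording, and the missing at-risk mean.

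A reader might infer three stronger things that the documents do not support.

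- *That the primary test is wrong.* No analysis is designated primary.
- *That the exercisers are shown to include non-drinkers.* The sentence beginning "Participants with no recent alcohol use had miR-133a (muscle enriched" reports Phase 1, and recent use there is defined by PEth, not by at-risk status. The mixed sample follows from Table 1 and the stated expectation.
- *That pooling cuts power from 80% to about 35%, or that a significant pooled result would probably be driven by others while at-risk drinkers gain nothing.* The 80% would need all 33 completers to be at-risk; the fair comparator is 54–56%. A response only in the others reverses the article's own expectation, and no passage supports an effect size for it.

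**Conclusion.** The point holds as a mismatch between the population claimed and the population analysed. Followed as written, the plan would attach a mixed-population estimate to at-risk drinkers, and no stated analysis gives their mean change. This rests on the text and does not depend on the illustrative figures.

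The size is uncertain. It depends on an at-risk share borrowed from the parent cohort, an interim count of 33 completers and an assumed response in the others. The bias is zero if both groups respond equally. The data needed are collected and the model is largely planned, so nothing is lost if this is settled before analysis. It should be settled then, because it changes what the trial can conclude about its named population.

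**What to change.** - **Definition.** Before analysis, set one baseline definition of at-risk use, as an AUDIT cut-off. The article gives none, so the sponsor must state it.
- **Model.** Use the planned regression of change with an at-risk indicator and the baseline outcome value. Centre the covariates at stated values so that the at-risk mean can be interpreted. Report the mean pre-post change in at-risk participants with its interval, the mean in the others, and the difference. Do not rely on centred AUDIT alone: its intercept is the change at average AUDIT, which is essentially the pooled mean again.
- **Conclusions.** Base any statement about at-risk drinkers on the at-risk estimate. Label the all-participant paired test as applying to PLWH with fasting dysglycemia and any alcohol use.
- **Wording.** Correct the population wording in the abstract, the Background sentence and the Discussion to match.

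The cost is analysis-plan and text changes only, since AUDIT is already collected. The statistical price is the wider interval in Step 5. The contrast between groups will be weak: with 19 and 14 participants, about 1.02 SD is needed for 80% power. A non-significant difference should therefore not be read as equal response.

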Evidence suggests that people engaging in regular aerobic exercise preserve or improve glycemic control, cardiovascular function, skeletal muscle function, have reduced risk of metabolic syndrome, and improved quality of life [22, 23]. Specifically, structured walking for approximately 30 min three times per week reduces fasting glucose, hemoglobin A1c, and HOMA-IR [24, 25]. Moreover, PLWH engaging in exercise have increased energy, improved self-concept, increased physical fitness, mental health, improved cardiometabolic measures, body composition and immune function [23, 26–30]. Studies show that moderate intensity exercise (40–60% heart rate reserve [HRR]) improves mitochondrial dysfunction, insulin resistance and diabetes among PLWH [31]. Additionally, our studies in the preclinical SIV model provided evidence that ex vivo β2 adrenergic stimulation of muscle myoblasts improved mitochondrial bioenergetics and mitochondrial copy number [21] supporting the hypothesis that aerobic exercise may improve mitochondrial homeostatic mechanisms resulting in improved glycemic control. Despite compelling evidence that exercise can be an effective strategy to improve metabolic health, little is known of how exercise improves metabolic health in PLWH, particularly those with at-risk alcohol use.

Based on our preclinical and clinical observational studies and evidence from the literature, we launched the Alcohol & Metabolic Comorbidities in PLWH: Evidence Driven Interventions Study (ALIVE-Ex Study, NCT03299205). This is an ongoing longitudinal prospective, interventional study investigating the effects of aerobic exercise in PLWH with fasting dysglycemia and at-risk alcohol use. The study consists of two phases. The objective of the first phase was to determine whether PLWH with at-risk alcohol use had increased risk of dysglycemia and dysregulated muscle metabolic function. The overall objective of the second phase of the study is to determine whether moderate intensity aerobic exercise will improve measures of whole-body glucose insulin dynamics and improve skeletal muscle metabolic and bioenergetic function. The secondary objective of Phase 2 is to determine whether the exercise intervention improves cognitive function and overall quality of life.

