### Outcome measures

#### OGTT

Outcome measures are determined as previously described [32]. Briefly, plasma glucose is measured at 0, 1 and 2 h using a glucose Analox analyzer (GM7 Analox microstat, Analox Instruments, USA) and area under the curve calculated. Plasma insulin and C-peptide are measured at 0, 1 and 2 h using ELISAs (Millipore Human Insulin ELISA, cat.no. EZHI-14 K; Alpco C-Peptide ELISA, cat.no. 80-CPTHU-E10.1). HOMA-IR is calculated (fasting glucose (mg/dL) x fasting insulin (µU/mL) divided by 405) and HOMA-β is calculated as 60 × fasting insulin (μU/mL) / (fasting glucose (mg/dL)—63). High molecular weight adiponectin is measured in the baseline samples using an ELISA (Alpco HMW Adiponectin ELISA, cat.no. 80-ADPHU-E01).

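### The primary outcome is an unranked bundle of three domains, worded differently in two places and tested at one unadjusted p < 0.05, so an error rate of 5% cannot be attached to a claim of primary success

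*Protocol article*

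**What the plan says.** The Abstract (Methods) gives the primary outcome as whether exercise "improves measures of whole-body glucose-insulin dynamics, cardiorespiratory fitness, and skeletal muscle metabolic and bioenergetic function". The last paragraph of the Background gives the overall Phase 2 objective as whether "moderate intensity aerobic exercise will improve measures of whole-body glucose insulin dynamics and improve skeletal muscle metabolic and bioenergetic function". Fitness is in the Abstract's statement and not in the Background's. Neither names a measure.

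The measures appear under Fitness assessment and in the subsections of Outcome measures. For the OGTT alone, "plasma glucose is measured at 0, 1 and 2 h using a glucose Analox analyzer" with an area under the curve, "Plasma insulin and C-peptide are measured at 0, 1 and 2 h using ELISAs", and HOMA-IR and HOMA-β are derived. The Secondary outcomes subsection holds only alcohol use, diet, cognition, anxiety and depression, and quality of life. The metabolic, fitness and muscle measures are therefore left in the primary set by default.

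Data management and analysis says that changes in outcome measures "between pre and post exercise intervention will be tested using the paired t-test". Its examples include OGTT outcomes, bioenergetic measures, microRNA expression, resting heart rate and VO2max. For 2-h glucose, HOMA-IR and HOMA-β, "clinical cutoff values will also be used". The section closes with "A p < 0.05 will be used for statistical significance".

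**The concern.** A 5% threshold limits the error of one prespecified test. Here it is attached to each of many measures, while the claim of interest (exercise improves the primary outcome) belongs to the bundle. With no deciding measure, no order and no statement of how many measures must succeed, the report can rest on whichever measure reached significance, and its error rate is then not 5%.

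The two wordings add to this. Whether a change in VO2max counts as a primary result depends on whether the reader takes the Abstract or the Background. The Abstract says that the results will demonstrate the effect of exercise on glycemic measures, so the trial is presented as more than exploratory.

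**Working it through.** The article gives no family-wise error rate and no number of primary measures, so there is no figure of its own to reproduce.

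**Step 1: count the measures** (inferred from the sections named).

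| Domain | Measures | Count |
|---|---|---|
| Glucose-insulin (OGTT) | glucose at 3 times + AUC (4); insulin and C-peptide at 3 times each (6); HOMA-IR, HOMA-β (2) | 12 |
| Fitness | VO2max, METs, resting heart rate | 3 |
| Muscle, function | glycolytic function, capacity, reserve (3); mitochondrial volume (1); at least 1 OCR parameter | 5 |
| Expression | at least 2 in muscle (genes, microRNAs); at least 1 circulating microRNA | 3 |

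Without expression measures: 12 + 3 + 5 = 20. With them: 23, or 22 if circulating microRNAs are left out. The wall push-up test, the cutoff-based analyses and any further OCR parameters, genes or microRNAs are not counted.

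**Step 2: independent tests, no true mean change.** The chance of at least one p < 0.05 in k tests is 1 − 0.95^k. Sidedness is not stated. Taking the tests as two-sided, the chance of at least one false result in the beneficial direction is 1 − 0.975^k.

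- k = 20: 1 − 0.95^20 = 0.642; 1 − 0.975^20 = 0.397
- k = 23: 1 − 0.95^23 = 0.693; 1 − 0.975^23 = 0.441
- k = 16 (the 20 less AUC, HOMA-IR, HOMA-β and METs, as overlapping): 1 − 0.95^16 = 0.560; 1 − 0.975^16 = 0.333

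**Step 3: correlated tests.** The documents give no correlations, so these are assumptions. Paired t-tests were simulated under a global null with n = 33 (the completers as of November 2022) and 10,000 runs. The measures formed three blocks (12/3/8 for k = 23, 12/3/5 for k = 20), each measure oriented so that benefit is positive. Between-domain correlation is 0 unless shown.

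| Within-domain r | k = 23, any | k = 23, beneficial | k = 20, any | k = 20, beneficial |
|---|---|---|---|---|
| 0.3 | 64% | 38% | 60% | 35% |
| 0.5 | 56% | 32% | 51% | 29% |
| 0.7 | 46% | 26% | 43% | 23% |
| 0.7 (between 0.3) | 42% | 22% | 40% | 20% |
| 0.9 | 31% | 16% | 29% | 16% |

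Across Steps 2 and 3 the range is about 29% to 69% for any significant result and 16% to 44% for a false improvement.

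**Step 4: comparison.** One prespecified measure at 0.05 has error 5%. One measure per domain, unadjusted and independent, gives 1 − 0.95^3 = 0.143. A fixed sequence at 0.05 holds the three at 5%, because each later test is made only if the one before it succeeds.

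**The case against.** Several arguments limit the point.

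- **A reader might infer that a false primary success is more likely than not.** The figures do not support that. The chance of any significant result falls below one half at within-domain correlations of about 0.7 or more. High correlation is plausible for parts of the OGTT set, where AUC and the HOMA indices are computed from other listed values. The aim is improvement, so significant worsening is not a success, and for false improvements alone the chance stays below one half at 20 to 23 measures even under independence.
- **A reader might infer that the plan declares any one significant measure sufficient.** It does not. It states a test and a threshold and is silent on what counts as success. The defect is that silence.
- **The count is a reconstruction.** Gene expression and circulating microRNAs are nowhere labelled primary, and the plan allows transformation, categorisation or non-parametric tests in place of the t-test. This stands, but 20 measures remain without any expression measure, and the data-dependent alternatives do not reduce the number of tests.
- **A multiplicity rule may sit in an analysis plan that is not shown.** This is fair, and the absence of an adjustment method is not the point. Naming the primary outcome is the protocol's job, however, and an analysis plan that picked one measure would have to depart from the Abstract's definition.
- **The difference between Abstract and Background is editorial.** In part: fitness is measured and tested under either wording. It still decides whether fitness is a primary result.

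**Conclusion.** The point holds as a defect in how the article fixes its primary outcome: a three-domain bundle with no deciding measure, a different set of domains in the Background, and one unadjusted threshold for all. If a single significant measure were reported as primary success, which the text does not rule out, the error rate would be roughly 30% to 70% for any significant result, against 5%. For a result in the beneficial direction it would be roughly 16% to 44%, against 2.5%. These ranges rest on an inferred 20 to 23 measures, two-sided tests, no true mean change in any measure, and assumed within-domain correlations from 0 to 0.9. The inflation is several-fold throughout, so the conclusion does not depend on where in the range the truth lies. It should be corrected before the final analysis.

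**What to change.** 1. Name one glycemic measure as primary, tested at 0.05. Change in 2-h OGTT glucose is one candidate. The Results section lists it among several measures that Phase 1 linked to at-risk alcohol use, with fasting C-peptide and HOMA-β. If it is chosen, state that it is analysed as continuous, since Data management and analysis now lists it among variables handled with cutoffs.
2. Then test one fitness measure (for example VO2max) and one named bioenergetic measure in fixed order, each at 0.05 and only if the preceding test succeeded.
3. Report all other OGTT, fitness, muscle, gene and microRNA measures as exploratory, with false-discovery-rate control.
4. Use the same primary in the Abstract and in the Phase 2 objective.
5. Make and document the choice without reference to the post-intervention data already collected from the 33 completers, and state that it was made after enrolment began. This matters because the limitations section already mentions a pilot data analysis, so a choice made now could otherwise be informed by results.

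The change is one of wording and needs no new data. Its price is that fewer measures can be called confirmatory, and that a late choice of primary carries less weight than one made before enrolment.
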